### Participant timeline {13}

#### Information briefing (> D7 before V0)

The investigator (psychiatrist) will offer patients the opportunity to participate in the study during a routine consultation, providing full details about the study procedure: the nature of the study, the objectives of the therapy, and the reasons for the indication. They will give the information leaflet entitled “Information leaflet for adult patients” to the patient which consists of information on the trial, with a consent form. For patients under guardianship, information adapted to their capacity to understand will be given. If the guardian is absent during this visit, the study information document can be sent to them by e-mail or by post by the physician. The guardian will be invited to accompany the patient to the inclusion visit so that the investigator can give them the information in person and answer any questions they may have. Consent may be signed by the guardian prior to the inclusion visit (V0), if the guardian agrees to the person’s participation. The patient/tutor/guardian will be informed that they will not be allowed to participate in an interventional study involving psychotherapy or an experimental drug for the duration of their participation in the protocol. The patient/tutor/guardian will be informed about the importance not to disclose their assigned treatment group to the psychiatrist involved in the recruitment process during their participation in the study, in order to keep the psychiatrist blinded for post-treatment evaluations using the BPRS and the Mini-FROGS. The patient/tutor/guardian is free to accept or reject the offer to participate. They will be given sufficient time (7 days minimum) to think over their decision.

### Inclusion visit (V0)

The first appointment at the hospital center is organized with the person (and the tutor/guardian, if applicable) to provide all necessary information about the intervention. The investigator answers all the questions the patient might have. The eligibility of the patients (inclusion and non-inclusion criteria) will be carried out by the psychiatrists in each center. The following routine evaluations will be conducted: intellectual disability estimated via the fNART, severity of self-stigma estimated by the ISMI, and severity of mental illness via CGI score.

Individuals with scores as indicated below will be included in the study; an inclusion number will be allocated to the patient:• ISMI self-questionnaire score ≥ 2• IQ > 70• CGI-Severity score < 6

Following this and if they meet the eligibility criteria and they agree to participate in the study, the patient may sign the consent form. The consent of the subject under guardianship will also be sought to the extent that their condition permits, and their refusal or revocation of acceptance will not be overridden. The patient/tutor/guardian will be given a copy of the informed consent.

The date on which the person agrees to participate in the research is noted in their medical record, as well as the date on which they object to participation, if applicable.

### Randomization

The investigator (psychiatrist) will then confirm the eligibility of the patient to another investigator (psychologist or nurse) of their team, who will be in charge of the randomization of the patients on the CleanWEB platform. This will ensure a blind assessment of the post-treatment evaluation by the psychiatrist at V1 and V2 (i.e., the BPRS and Mini-FROGS scales).

Patients will be randomized by the psychologist or the nurse into one of the following arms:Experimental arm: 12 week-treatment of compassion-focused therapy (CFT) (i.e., psychoeducation on the model, experiential in-session exercises, and in-between session compassion practices, video-guided practices). Sessions cover several topics: psychoeducation on compassion from an evolutionary and neuroscientific perspective, emotion regulation skills (especially shame), and compassion practices.Active control arm: 12 week-treatment of the psychoeducation program *Ending Self-Stigma* (ESS) [29]. Sessions cover topics such as modifying self-stigmatizing thoughts and homework.Passive control arm: patients follow their usual care, i.e., TAU (e.g., psychiatric, psychological, day hospital), which will be unchanged during the 12-week period. Following their 10-month participation in the study, they will be given access to the written material used for the ESS.

Participants will then be asked to complete self-report questionnaires assessing self-compassion, shame, depression, anxiety, barriers to care, social functioning, recovery, and functional remission. During this visit, the cognitive task assessing avoidance/approach attitudes toward mental illness (VAAST) will also be carried out by the psychologist or the nurse.

Two individual sessions with a clinician (engagement phase) will be conducted between V0 and the beginning of CFT and ESS (i.e., within 1 month). These sessions will include motivational interviewing techniques and case conceptualization aimed at increasing the participant’s level of engagement in therapy.

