To evaluate the *acceptability* of the active interventions (CFT and ESS):• The Credibility and Expectations Questionnaire [68, 69] will be applied to assess self-reported treatment credibility at V0. This questionnaire contains 6 items rated either from 1 to 9 or from 0 to 100% and evaluates whether the participants “think” or “feel” that their treatment will be efficient.• The Group Questionnaire [70] will be used to measure group cohesion 3 times during the intervention (sessions 1, 6, and 12). It consists of 30 items addressing the group leaders, the other group members, and the group in general. Each item is scored using a scale ranging from 1 (not true at all) to 7 (very true).• The Consumer Satisfaction Questionnaire for Psychotherapeutic Services (CSQ-8) [71] will be applied as a self-report measure assessing participants’ satisfaction at the end of the 12-week program. The 8 items are scored on a scale ranging from 1 to 4. Higher scores are indicative of elevated satisfaction.• The attendance rate will be determined by the number of group sessions attended by the patient, and the drop-out rate will be determined by the number of patients lost to follow-up in each arm. In addition to the Consumer Satisfaction Questionnaire for Psychotherapeutic Services questionnaire (CSQ 8) [71], the avoidance of participants (due to self-stigma) in several social situations during the last 6 months, and the satisfaction with the interventions will be assessed via semi-structured interviews conducted at V2 by clinician-researchers blind to the status of patients (in the Strasbourg center only, for the 3 groups—CFT, ESS, and TAU).

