### Assignment of interventions: allocation

#### Sequence generation {16a}

Randomization will be done through the CleanWEB® platform, which will be accessed by the investigator or a designated person, using their personal access codes. The investigating team and the sponsor will receive an email confirming the randomization. Patients will be randomized over a period of 1 month before the start of the interventions, to allow the 3 groups of treatment to be formed (CFT, ESS, TAU), so that each group starts the allocated therapy at the same time.

The randomization will be stratified by center, with a 1:1 ratio for allocation to the 3 groups. Patients will be recruited until they form a group of 24 people allowing to randomize them in one of the 3 conditions, in groups of 8 people matched on gender and diagnostic group (4 possibilities: (1) psychotic disorder, (2) mood disorder, (3) personality disorder, and (4) autism spectrum disorder, referring to (1) schizophrenia-spectrum disorder, (2) bipolar disorder and depression, (3) borderline personality disorder, and (4) autism spectrum disorder). This process will be reiterated at least once in each center:

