### Assignment of interventions: blinding

#### Who will be blinded {17a}

Participants will be informed of the group which they are allocated to. Care providers are informed of which treatment group they are facilitating. The psychiatrist performing the clinical examination and assessing the outcomes (at V0, V1, V2) is not involved in the randomization process and remains blind to the groups to which patients are attributed throughout the trial. The allocation sequence is configured by our data manager who is blinded to the allocation group.

In the Strasbourg center only, the clinical psychologist administrating the semi-structured interview will be blinded to the experimental arm of the patient (i.e., a clinical psychologist not involved in the trial to make sure that they had no previous contact with the participant).

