### Procedure for unblinding if needed {17b}

The design is open-label with only outcome assessors and the clinical psychologist performing the semi-structured interviews being blinded so unblinding will not occur.

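### As written, the V0 self-reports and the VAAST follow randomisation in an open-label trial, so several secondary-outcome baselines and at least two of the three mediator baselines can reflect knowledge of the arm

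*Protocol article*

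**What the plan says.** All references are to the protocol article.

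The Inclusion visit (V0) section places the fNART, the ISMI and the CGI first, then the eligibility decision and consent. The Randomization section continues from there. Eligibility is passed to a second team member, and "Patients will be randomized by the psychologist or the nurse into one of the following arms". After the description of the three arms it says: "Participants will then be asked to complete self-report questionnaires assessing self-compassion, shame, depression, anxiety", and the list goes on to recovery, functional remission, social functioning and barriers to care. It adds that at this visit "the cognitive task assessing avoidance/approach attitudes toward mental illness (VAAST) will also be carried out by the psychologist or the nurse".

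On blinding, Who will be blinded {17a} says "Participants will be informed of the group which they are allocated to", and section {17b} says "The design is open-label with only outcome assessors and the clinical psychologist performing the semi-structured interviews being blinded". The Secondary outcomes section has a questionnaire that "will be applied to assess self-reported treatment credibility at V0".

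Sequence generation {16a} describes allocation differently: "Patients will be recruited until they form a group of 24 people allowing to randomize them in one of the 3 conditions".

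The Objectives {7} and Secondary outcomes sections treat V0 as the baseline for shame, self-compassion, emotional regulation, avoidance tendencies, symptoms and functioning. Statistical methods {20a} names self-compassion, shame and emotional dysregulation as the candidate mediators.

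**The concern.** A baseline protects a randomised comparison because allocation cannot have influenced it. Here the stated order is randomise first, then measure. Most of the measures are subjective ratings by people who are not blinded: some have just been given a place in a new therapy group, others have been assigned to continue usual care.

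If their answers move in response, the V0 value is no longer a clean starting point. Any analysis that subtracts it or adjusts for it carries the movement into the treatment contrast. At stake are the secondary outcomes in the listed battery and the mediation analysis, in which shame is the trial's main mechanistic hypothesis. No later analysis can recover a pre-allocation value that was never collected.

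**Working it through.** **Order of events.**

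| Step | Source section | Position relative to randomisation |
|---|---|---|
| fNART, ISMI, CGI, eligibility, consent | Inclusion visit (V0) | before |
| Randomisation on CleanWEB by psychologist or nurse | Randomization | – |
| Self-reports: self-compassion, shame, depression, anxiety, barriers to care, social functioning, recovery | Randomization | after |
| VAAST, run by psychologist or nurse | Randomization | described after, same visit |
| Two engagement sessions, then therapy within 1 month | Randomization | after |

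The battery list also names functional remission as self-report, whereas Secondary outcomes has it rated by a clinician-researcher. It is left out of this point. Emotional dysregulation (DERS-16) is not in the list, so the order is explicit for two of the three mediators.

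**Does the participant know the arm by then?** The moment of disclosure is not stated. Three things point to V0: participants are told their group, the battery is placed after randomisation, and treatment credibility is rated at V0. The concealment section ties release of the code to recruitment into the trial, not to completion of the baseline measures. Knowledge of the arm while answering is therefore an inference, but nothing in the article prevents it.

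**Does Sequence generation {16a} change the order?** It gathers 24 patients and then randomises them. That does not fit randomisation within each patient's V0. If it governs, the V0 measures could come first, but the section does not mention the battery. The two sections conflict, and the conflict does not settle the order in favour of a clean baseline.

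**Illustration of size.** The article gives no figure to reproduce here. The shift s and the baseline-to-follow-up correlation ρ are assumed. n = 84 per arm is the pre-inflation size in Sample size {14}. The model has equal SDs, a shift in the baseline only, no true effect, no clustering, and a two-sided 5% test as a stand-in for the 0.975/0.025 posterior rule.

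- Change score: bias = s; SE = √(2(1−ρ)) × √(2/n)
- Baseline-adjusted: bias = ρs; SE = √(1−ρ²) × √(2/n)
- Chance of excluding zero = Φ(bias/SE − 1.96) + Φ(−bias/SE − 1.96)

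Worked case, s = 0.2 and ρ = 0.5: √(2/84) = 0.1543.

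- Change score: SE = 1 × 0.1543 and 0.2/0.1543 = 1.296, giving Φ(−0.664) + Φ(−3.256) = 0.254.
- Adjusted: bias = 0.10, SE = 0.866 × 0.1543 = 0.1336 and 0.10/0.1336 = 0.748, giving Φ(−1.212) + Φ(−2.708) = 0.116.

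| s (SD) | ρ | Change-score bias | Zero excluded | Adjusted bias | Zero excluded |
|---|---|---|---|---|---|
| 0.1 | 0.5 | 0.10 | 9.9% | 0.05 | 6.6% |
| 0.2 | 0.5 | 0.20 | 25.4% | 0.10 | 11.6% |
| 0.3 | 0.5 | 0.30 | 49.4% | 0.15 | 20.2% |
| 0.1 | 0.7 | 0.10 | 13.3% | 0.07 | 9.7% |
| 0.2 | 0.7 | 0.20 | 38.7% | 0.14 | 24.6% |
| 0.3 | 0.7 | 0.30 | 70.9% | 0.21 | 47.8% |

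**Direction.** Take shame, where higher is worse. Disappointment raises the TAU baseline and hope lowers the CFT baseline, so the CFT-minus-TAU baseline difference is −s. With a true CFT benefit of δ SD, the change-score contrast estimates δ − s and the adjusted contrast δ − ρs. The named reactions therefore shrink CFT's apparent advantage over TAU. Under no true effect, the excess in the table lies almost wholly on the side against CFT.

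**The case against.** The strongest reply is that the order hangs on one word in a narrative paragraph. Batch randomisation could put every baseline first, and the schedule table and flow chart, which might settle the matter, are not available here. The V0 credibility rating shows knowledge of the arm at some time in that visit, not necessarily before the battery. This lowers the certainty that sites would in fact measure after disclosure. It does not remove the point: the only text that places the battery puts it after randomisation, and if site practice differs, that text is wrong.

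Several stronger readings are tempting, and the article does not support them:

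- *The primary result is at risk.* It is not, on this ground. The ISMI is taken for eligibility before randomisation, so both the primary outcome and the 6-month ISMI have a clean baseline. For the same reason, the planned CFT–ESS difference on the ISMI is no yardstick for this bias.
- *Every self-report secondary outcome and all three mediators are affected.* The 6-month ISMI is not, and the order is not stated for emotional dysregulation.
- *Staff who know the arm administer the whole battery.* This is stated only for the VAAST. Self-reports are completed on a tablet.
- *Clinician ratings are affected.* They are made by a psychiatrist who remains blind at V0, V1 and V2.
- *The order could manufacture a CFT benefit.* The plausible reactions work against CFT relative to TAU. CFT and ESS share format and length, and nothing in the article suggests different reactions to those two allocations.

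It is also fair to say that open-label self-reports at V1 and V2 carry expectation effects whatever the V0 order. That is a separate matter and no reason to leave the baseline exposed as well.

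**Conclusion.** The point holds as a risk created by the stated order and should be fixed. If the Randomization section is followed as written, the V0 values of the listed self-reports and the VAAST are post-allocation measurements in an open-label trial. They then cannot safely serve as baselines for those secondary outcomes or for shame and self-compassion as mediators. Treatment exposure is not the issue, because the battery is described before the engagement sessions.

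The size is unknown. The shifts of 0.1 to 0.3 SD and correlations of 0.5 to 0.7 are assumptions. So is the use of change scores or baseline adjustment, since Statistical methods {20a} does not say how V0 enters the secondary or mediation models. The most plausible consequence is an understated effect of CFT against TAU on these outcomes. Confidence is high that the text gives this order and conflicts with Sequence generation {16a}, and moderate that participants would know their arm while answering.

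**What to change.** In the Randomization section, state that all V0 self-reports (including the DERS-16, whose position is not given) and the VAAST are completed and locked before CleanWEB randomisation. If that cannot be arranged, they should at least be complete before the arm is disclosed to the participant. Only the Credibility and Expectations Questionnaire, which asks about the assigned treatment, should follow allocation.

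Reconcile this section with Sequence generation {16a}, so that both say whether patients are randomised one by one at V0 or as a batch of 24. With batch randomisation, a natural rule is to release the block once all its V0 records are locked.

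The cost is a re-ordered visit and a completeness check. Self-reports are held in Limesurvey and randomisation runs in CleanWEB, so the check needs a confirmation field in CleanWEB or a link between the two systems. No new measure or extra visit is needed. The Trial status section says enrolment had not started, so the change could be made before any baseline was collected.

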### Experimental or control therapies (12 weeks)

Participants randomized to the experimental arm and the active control arm will begin the intervention (CFT or ESS) within 1 month, to allow for the formation of a group of 8 individuals for each active arm. Participants randomized to the TAU arm will pursue their routine care.

Both therapies (CFT and ESS) will follow the same modalities: groups of 8 patients, facilitated by 2 co-therapists (one senior psychologist and one mental health professional or peer support worker). Sessions will have a duration of 2 h including a 15-min break, therapy manuals and a whiteboard will be used and both therapies will include homework practices.

### Follow-up visit V1 (end of treatment + 1 week)

This visit corresponds to the end-of-treatment assessment (T1) for patients in each arm, starting at week 18 after inclusion (following the last group session for the active arm and the active control arm). This evaluation includes the administration of the self-report questionnaires, including the ISMI, and the administration of the cognitive task (VAAST). A psychiatrist blinded to the experimental arm of the patient will conduct an evaluation of psychiatric symptoms and functional remission via the BPRS and the Mini-FROGS.

### Follow-up visit V2 (end of treatment + 6 months)

This visit corresponds to the follow-up assessment (T2) for patients of each arm, starting 6 months after the last group treatment session (and 9 months after the inclusion of the TAU group). This evaluation includes the administration of the self-report questionnaires, including the ISMI, the administration of the cognitive task (VAAST). A psychiatrist blinded to the experimental arm of the patient will conduct an evaluation of psychiatric symptoms and functional remission via the BPRS and the Mini-FROGS**.**

Moreover, in the Strasbourg center only, a semi-structured interview will be led by a clinical psychologist blinded to the experimental arm of the patient (i.e., a clinical psychologist not involved in the trial to make sure that they had no previous contact with the participant). The interview will assess the avoidance of participants (due to self-stigma) in several social situations as well as their satisfaction with the intervention (CFT and ESS).

An additional 1-month window will be allowed to conduct this visit. The participation of patients ends at the end of this visit (Fig. 1). Table 3 shows the schedule for the COMPASS study.

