## Passive control arm (TAU)

Participants will not participate in any intervention aimed at reducing self-stigma. They will continue their usual treatment which might include weekly visits to their psychiatrist. Participants and therapists in each center will receive, after the study period, access to the ESS notebook.

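### The V2 interviewer is declared blind to arm without limit, but the interview also covers satisfaction with CFT or ESS, so blinding cannot last throughout and is not protected for the avoidance part

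*Protocol article*

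**What the plan says.** The protocol article states the interviewer's blinding in four places.

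- *Secondary outcomes* (acceptability) describes "semi-structured interviews conducted at V2 by clinician-researchers blind to the status of patients (in the Strasbourg center only, for the 3 groups", that is CFT, ESS and TAU.
- *Follow-up visit V2* says that "a semi-structured interview will be led by a clinical psychologist blinded to the experimental arm of the patient", and explains the safeguard as "a clinical psychologist not involved in the trial to make sure that they had no previous contact with the participant".
- *Who will be blinded {17a}* repeats that "the clinical psychologist administrating the semi-structured interview will be blinded to the experimental arm of the patient".
- *Procedure for unblinding if needed {17b}* counts this psychologist among the blinded persons and concludes that no unblinding will take place.

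The content of the interview is given in *Follow-up visit V2*: it assesses avoidance of social situations due to self-stigma "as well as their satisfaction with the intervention (CFT and ESS"). *Secondary outcomes* lists the same two topics. *Lexical/semantical analyses* plans a software analysis of 48 interviews, in which relative word occurrences are compared between subgroups with a chi-square test.

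**The concern.** Blinding can be lost before an interview or during it. The stated safeguard, an interviewer from outside the trial who has never met the participant, deals only with the first. The second topic invites participants to talk about the programme they attended, and they are not blind themselves. A claim of blinding that covers the whole interview therefore conflicts with what the interview is meant to collect.

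At stake is the avoidance material. In a semi-structured interview, follow-up questions depend on the interviewer's judgement and shape how much is said and in which words. An interviewer who knows the arm can probe differently, and those words are what the lexical analysis counts. The trial report could then describe as blinded an assessment that was not, or not reliably so.

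**Working it through.** No formula applies and the plan gives no figure to reproduce. The check sets the relevant sections side by side.

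1. **Does the participant know the arm?** Yes. *Who will be blinded {17a}* says that participants are told their group.
2. **Are all arms interviewed?** Yes, in Strasbourg (*Secondary outcomes*).
3. **Does the satisfaction topic separate TAU from the active arms?** Yes. Of TAU, *Passive control arm (TAU)* says: "Participants will not participate in any intervention aimed at reducing self-stigma". Satisfaction is to be assessed for CFT and ESS, so whether the topic applies at all shows whether the person was in an active arm.
4. **Does it separate CFT from ESS?** Very likely, once the programme is discussed. Table 1 gives CFT distinctive content (soothing rhythm breathing, compassionate-self imagery). Table 2 does the same for ESS (the 3C's strategy). This step is reasoned from the session contents; the document does not state it.
5. **Do the safeguards cover disclosure during the interview?** No. Lack of previous contact prevents prior knowledge only. The instruction to patients in *Information briefing* not to reveal their group names the psychiatrist involved in recruitment, and its stated purpose is to protect the BPRS and Mini-FROGS ratings. It does not name this interviewer. It could not cover the whole interview in any case, because the satisfaction part requires the participant to speak about the programme.
6. **Is the avoidance part shielded by its position?** Not by anything stated. Both descriptions mention avoidance first and satisfaction second, but neither says that this is the order of questioning or that the first part is closed before the second opens.

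**Scope.** *Recruitment {15}* gives blocks of 24 patients, in three groups of 8. *Lexical/semantical analyses* gives 48 interviews from the first two Strasbourg samples.

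- 48 / 24 = 2 blocks
- 2 × 8 = 16 interviews each in CFT, ESS and TAU, if both blocks are complete
- 16 + 16 = 32 interviews in active arms, against 16 in TAU

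All 48 are exposed to the problem once satisfaction is raised. How many would be unblinded earlier, while avoidance is being covered, cannot be derived from the document.

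**The case against.** The strongest reply is that the avoidance part may well be blinded in practice. Avoidance is named before satisfaction in both descriptions, and an interview guide or the full protocol may fix that order. A journal article is not expected to print the guide. This stands as far as it goes: a reader might infer that the avoidance assessment *is* unblinded, and the document does not support that. It supports only that its blinding is not protected. Nor is the absence of a topic order the finding in itself. The finding is that the published blinding statements cover the whole interview without qualification, and a fixed order would make them true for one part only.

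Three further inferences are tempting and should be resisted.

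- **A biased avoidance score.** No rating or scale for avoidance is described. The only analysis given is lexical, so the route for bias is questioning and probing, which is weaker than a biased rating.
- **A blinded check on the open-label self-reports.** The article does not give the interview that role. It calls the VAAST complementary in that sense. The interview sits under acceptability, and *Objectives {7}* describes the qualitative interviews as assessing acceptability of the active interventions.
- **192 affected interviews.** That is the Strasbourg recruitment target. Only 48 interviews have a stated analysis.

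It is also fair to say that no efficacy conclusion turns on this point. The ISMI is self-reported in an openly unblinded design, and the BPRS and Mini-FROGS are rated by a psychiatrist whose blinding has its own safeguards.

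**Conclusion.** The point holds in a limited form. As written, *Secondary outcomes*, *Follow-up visit V2*, *Who will be blinded {17a}* and *Procedure for unblinding if needed {17b}* claim a property that the interview cannot have from start to finish. Blinding must end when satisfaction with CFT or ESS is discussed. For the avoidance part it is possible but unprotected.

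The size is small: one centre, one secondary interview outcome, 48 analysed interviews (16 per arm if the two blocks are complete). ISMI, BPRS and Mini-FROGS are not affected.

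The conclusion assumes that participants answer the satisfaction topic in enough substance to reveal their programme. The effect on the lexical comparison further assumes that the subgroups compared include the trial arms, which the article does not spell out. Severity is minor.

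**What to change.** 1. State that the avoidance part is completed and recorded before satisfaction is raised.
2. Extend the non-disclosure instruction in *Information briefing* to this interviewer, for the avoidance part only.
3. Restrict the blinding statements in the four sections named above to the avoidance part, including the statement that unblinding will not occur as far as it concerns this interviewer.
4. Run the lexical comparison of avoidance on that section of the transcript only, so that talk about the programme does not enter it.

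If this is not wanted, drop the blinding claim for this interview and report it as unblinded.

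The cost is a fixed interview order, which gives up some of the flexibility of a semi-structured format, a narrower blinding claim, and dividing each transcript at the change of topic. Sample size, visits and the primary analysis stay as they are.
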